## Abstract

**Background:**

Cystic fibrosis is an inherited disease, which is caused by the CFTR protein defects due to mutations in the CFTR gene. Along with CFTR dysfunction, exocrine pancreatic insufficiency plays a key role in persistent fat malabsorption in CF patients; therefore, deficiency of fat-soluble vitamins (A, D, E, and K) is still a therapeutic challenge. Even with efficient pancreatic enzyme medication and CF-specific vitamins, many patients with CF have fat-soluble vitamins deficiency. The present study aims to evaluate the efficiency of nanomicelle formulation of fat-soluble vitamins in children with CF in order to achieve the appropriate serum levels of these vitamins.

**Methods:**

This prospective, single-blind control trial will be conducted at the Akbar Children’s Hospital in Mashhad, Iran. Patients with CF will be enrolled based on the eligibility criteria. The control group will receive the standard formulation of fat-soluble vitamins similar to the routine CF treatment, and for the intervention group, the nanomicelle formulation of fat-soluble vitamins will be administered for 3 months. The primary outcome of this study is the measurement of serum levels of fat-soluble vitamins. The secondary outcomes are clinical assessment by the Shwachman-Kulczycki score, anthropometrics, and quality of life. Outcomes will be assessed before and after 3 months.

**Discussion:**

Due to persistent fat-soluble vitamin deficiency in CF disease, the nanomicelle formulation could be proposed as a new delivery method of fat-soluble vitamins in the treatment of cystic fibrosis.

**Trial registration:**

Iranian Registry of Clinical Trials IRCT20220415054541N1. Registered on July 23, 2022.

## Introduction

### Background and rationale {6a}

Cystic fibrosis (CF) is a life-shortening, autosomal recessive genetic disorder, and the most common inherited disease in Caucasians. The disease prognosis has improved considerably in recent decades with the advanced treatments, and the mortality rate has been reduced by 2% annually. The average age of survival in CF patients has been reported to be 65 years in men and 56 years in women [1]. CF is caused by mutations in the cystic fibrosis transmembrane conductance regulator (CFTR) gene, resulting in impaired pancreatic function and, as a result, reduced intestinal absorption of lipids and fat-soluble vitamins, particularly in patients with CF developing pancreatic insufficiency [2]. Fat-soluble vitamins deficiency is still a current therapeutic challenge in CF, chronic pancreatitis, and biliary atresia. A large number of patients exhibit vitamin K or D insufficiencies, and the prevalence of vitamin E and A deficiencies is also significant despite full compliance [3]. In many cases, increases in vitamin dosage are not efficacious, and intractable fat-soluble vitamin deficiencies are diagnosed in CF patients, raising the issue of whether modern drug delivery methods could improve the condition of patients [3, 4]. Although the standard formulation is still used in CF patients, there are new delivery technologies, such as the liposomal form of vitamin E, the nanomicelle form of curcumin, and specific carotenoids [5]. To improve stability and increase the solubility of fat-soluble or poorly water-soluble compounds, several strategies such as liposomal, nanoliposomal, and micellar forms have been recommended. One is using nanomicelles which are efficient tools to encapsulate the drugs with a low aqueous solubility [6]. The nanomicelle has a core-shell structure that prevents the penetration of water in its inner core creating an appropriate environment for the encapsulated drug versus the free drug [6]. Other advantages of micelles as drug carriers include facilitated transport through biological barriers, protection against degradation, being cost-effective, and increased solubility in aqueous media that include the unstirred water layer of the intestine [7]. Consequently, the concept of using the nanomicelle formulation of fat-soluble vitamins could be admirable in CF patients through the facility of absorption of nano-sized vitamins and the lack of necessity of the presence of pancreatic enzymes for their absorption process. In this study, we focused on a novel nanomicelle formulation of vitamins A, D, E, and K, and the main purpose was to address the problem of intractable fat-soluble vitamin deficiencies in pancreatic-insufficient CF patients. The present study aimed to evaluate the efficiency of the novel nanomicelle formulation of fat-soluble vitamins in CF (Table 1).

**Table 1 Tab1:**
[figure not shown]
Fat-soluble vitamins—classification, laboratory measurements, test equipment, normal range, deficiencies, and toxicities

### Objectives {7}

The present study aimed to evaluate the efficacy of the novel nanomicelle formulation of fat-soluble vitamins in CF patients to achieve the appropriate serum level of fat-soluble vitamins.

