### Outcomes {12}

The primary outcome of the current trial is the measurement of the serum levels of fat-soluble vitamins once at the onset of enrollment and once at the end of the trial after 3 months.

The secondary outcomes are clinical criteria evaluation by the Shwachman-Kulczycki score (an index to evaluate the severity of the disease in CF patients, which includes general activity, physical examination, nutrition, and radiological findings), anthropometric assessment by the BMI *Z* score, and quality of life evaluation by using the CFQ (Health-Related Quality of Life in Children with Cystic Fibrosis) from the baseline to 3 months of the intervention (Fig. 1).

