## Statistical methods

### Statistical methods for primary and secondary outcomes {20a}

SPSS will be used to analyze the data. The Kolmogorov-Smirnov test will be used to evaluate data distribution. The data are expressed as frequencies and percentages for the qualitative variables, the mean and standard deviation for the normally distributed continuous variables, and the median and interquartile range for the other variables. Additionally, intergroup differences will be evaluated using a paired *T*-test for the normally distributed continuous variables and the Wilcoxon rank-sum test for the other continuous variables. Intergroup differences will be assessed using an independent *T*-test for the normally distributed continuous variables and the Mann-Whitney *U*-test for the other quantitative variables. The mean changes in the secondary outcomes will also be adjusted using the analysis of covariance (ANCOVA). The *P* value of less than 0.05 will be considered significant in all the numerical analyses.

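### The objective is an appropriate serum level and the trial is sized on a vitamin D recovery proportion, but the analysis compares only raw serum levels

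*Protocol article*

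**What the plan says.** The Objectives section sets a target: the new formulation is to be evaluated for its ability "to achieve the appropriate serum level of fat-soluble vitamins". The abstract has the same aim: "in order to achieve the appropriate serum levels of these vitamins".

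The Sample size section works with a proportion. About 60% of patients on the routine formulation are taken to be treated for vitamin D deficiency, the new method is expected to raise the recovery rate by 30–40%, and 33 patients per group follow at alpha 0.05 and 80% power.

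The Outcomes section defines the primary outcome as "the measurement of the serum levels of fat-soluble vitamins once at the onset of enrollment and once at the end of the trial", three months later. It names no category of deficient, in range or above range.

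The Statistical methods section summarises data by "the mean and standard deviation for the normally distributed continuous variables, and the median and interquartile range for the other variables". For the comparison of arms it says: "Intergroup differences will be assessed using an independent *T*-test for the normally distributed continuous variables", with the Mann-Whitney test otherwise. Qualitative variables are described by frequencies and percentages, and no test of a proportion is named. The section on additional analyses lists the same tests.

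The caption of Table 1 announces "normal range, deficiencies, and toxicities" for the four vitamins. Neither the outcome section nor the statistical section uses these limits.

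**The concern.** Objective and sample size ask whether patients reach a level. Outcome and tests ask how far apart the raw levels of the two arms lie. These are different questions, and the gap has three consequences.

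1. The recovery proportion that justifies 33 per group is never compared between arms.
2. A significant difference in mean or median does not say how many children reached the appropriate range. Eligibility does not require a deficiency at entry, so a rise in children already in range also widens the difference.
3. A value above the upper limit moves the mean or rank comparison in the same direction as a value brought up into range. The formulation is meant to ease absorption without relying on pancreatic enzymes, so the number above range is a natural question. The trial measures the levels that would answer it, but no planned summary counts them.

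At stake is whether the final report can support a statement that appropriate levels were achieved.

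**Working it through.** **Step 1: the plan's own figure.** Inputs from the Sample size section: control proportion 0.60, alpha 0.05, power 80%, dropout 10%. My readings: 60% is the proportion recovered on routine treatment, the lower end of the 30–40% increase is absolute (0.90), and the test is two-sided.

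Pooled formula: n = [1.96·√(2·0.75·0.25) + 0.8416·√(0.60·0.40 + 0.90·0.10)]² / 0.30²
= [1.2002 + 0.4835]² / 0.09 = 2.835 / 0.09 = 31.5, so 32 per group.

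The plan states 33, so the figure reproduces to within one patient. Dropout: 33/0.9 = 36.7, so 37 per group and 74 in total, as stated. A relative reading (60% to 78% or 84%) would need 103 or 54 per group and does not reproduce it. The trial was therefore sized on a difference of two proportions.

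Power at 33 per group for 60% versus 90%: Φ[(0.30·√33 − 1.2002)/0.5745] = Φ(0.911) = 82%.

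**Step 2: what the planned test detects.** With 33 per group, a comparison of means has 80% power for a difference of (1.96 + 0.8416)·√(2/33) = 0.69 SD. This holds wherever the values lie relative to the normal range.

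**Step 3: how a mean shift maps to the range.** The documents give no means, SDs or range widths, so this is an illustration on assumptions: normal data, control SD 1, range from 0 to 3 (3 SD wide), and 40% of controls below range. The control mean is then 0.253 SD above the lower limit. For an arm with mean m and SD s: below = Φ(−m/s), above = 1 − Φ((3 − m)/s), within = the rest.

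| Arm | Below | Within | Above | At or above lower limit | Power of mean test, 33 per group |
|---|---|---|---|---|---|
| Control | 40% | 60% | 0.3% | 60% | – |
| Shift 1.03 SD, SD 1 | 10% | 86% | 4% | 90% | 99% |
| Shift 2 SD, SD 1 | 1% | 76% | 23% | 99% | over 99% |
| Shift 2 SD, SD 1.5 | 7% | 62% | 31% | 93% | over 99% |

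The shift of 1.03 SD is the one that takes the recovered proportion from 60% to 90% under these assumptions (1.282 − 0.253).

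**Step 4: sensitivity to range width.** Same 2 SD shift, equal SDs, 40% of controls below range:

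- range 2 SD wide: within range falls from 56% to 39%, with 60% above;
- range 3 SD wide: within range rises from 60% to 76%, with 23% above;
- range 4 SD wide: within range rises from 60% to 95%, with 4% above.

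The mean test is near certain to be significant in all three, so it cannot tell them apart.

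**The case against.** Several stronger readings are tempting, and the documents do not support them.

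- *A reader might infer that the plan counts above-range values as success.* It defines no success criterion and no direction of benefit. What holds is narrower: such values add to the arm difference.
- *A reader might infer that overshoot is likely, or that the in-range gain will be trivial.* No baseline mean, SD or range width is given. The smallest in-range gain in the Step 3 table, from 60% to 62%, needs a 50% larger SD in one arm. With equal SDs the same shift gives 76% within range. At the plan's own effect of 60% to 90%, it is 86% within and 4% above, and the mean and the proportions agree.
- *A reader might infer that the sample size already assumes an in-range endpoint.* Recovery from deficiency is a lower-limit criterion. It would not count overshoot either.
- *A reader might infer that a safety signal would be hidden.* A reported mean and SD set against the Table 1 limits would hint at overshoot. It would be uncounted, not concealed.

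Replacing the primary outcome with an in-range proportion is also debatable. It discards information, and it scores a child above range the same as one still deficient, although deficiency is the stated main problem. Serum level is a defensible primary measure.

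Finally, the contents of Table 1 are not shown, and range categories could be described under the qualitative variables or be set out in a fuller document. This softens the point about description. It does not supply a between-arm comparison of the sized proportion, because the tests named are for continuous data only.

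**Conclusion.** The mismatch stands in the text. The objective is a target level and the sample size is a recovery proportion, while the outcome and tests fix only raw levels. The proportion behind the 33 per group is never tested, although 33 per group gives 82% power for it at 60% versus 90%. A significant mean difference would not by itself support a claim that appropriate levels were reached.

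The size of any divergence is unknown. On the assumptions shown (normal data, range 3 SD wide, 40% of controls below range), it runs from 86% within and 4% above to 62% within and 31% above, and a narrower range makes it worse. This is a cheap and worthwhile improvement to the analysis. It gives no reason to discard the primary outcome.

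**What to change.** Keep the serum level as the primary outcome. In the Statistical methods section:

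1. Add a between-arm risk difference with 95% confidence interval for the proportion of randomised patients at or above the Table 1 lower limit for vitamin D at 3 months. This is the recovery proportion of the Sample size section.
2. For all four vitamins, report by arm the proportions below, within and above the Table 1 range at 3 months, with the above-range proportion as a safety summary.
3. State that any claim of achieving appropriate levels rests on these proportions and not on the mean difference alone.

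Cost: no new assays and a little more analysis. The binary comparison is less sensitive than the mean. At 60% versus 90% with 33 per group, the standard error is √(0.24/33 + 0.09/33) = 0.10, so the 95% interval is about ±20 points. The above-range proportion will be descriptive: 4% of 33 is about 1 patient, and 31% is about 10. The Trial status section reports that recruitment ended in November 2022, so the addition should be dated, and labelled post hoc if the data have already been seen.

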### Trial design {8}

This is a prospective, single-center, parallel, randomized placebo-controlled trial. The study protocol conforms to the Standard Protocol Items Recommendation for Interventional Trials (SPIRIT) Checklist (Table 2).

**Table 2 Tab2:**
[figure not shown]
Schedule of enrolment, intervention, and assessment based in the Standard Protocol Items Recommendations for Interventional Trials (SPIRIT) guideline

## Methods: participants, interventions, and outcomes

### Study setting {9}

The study population will comprise the known CF patients referred to the Cystic Fibrosis Clinic at Akbar Children’s Hospital, Mashhad, Iran.

### Eligibility criteria {10}

#### Inclusion criteria

The inclusion criteria of the study include (1) one or more typical phenotypic features of CF and a minimum of an elevated sweat chloride concentration on two/more occasions or two mutations known to cause CF on separate alleles, (2) age ≥ 8 years old, (3) gastrointestinal and pulmonary involvement, (4) the oxygen saturation percentage based on the pulse oximetry of ≥ 90% at room temperature, (5) a clinically stable situation, and (6) informed consent of the patient’s parents.

#### Exclusion criteria

The exclusion criteria of the study include (1) cardiovascular, renal, or hepatic impairment; (2) celiac disease; and (3) no adherence to drug consumption.

### Who will take informed consent? {26a}

Initially, the first researcher will clarify the study objectives to the children’s parents and legal guardians, and written informed consent will be obtained from them at the time of enrolment.

### Additional consent provisions for collection and use of participant data and biological specimens {26b}

In the consent form, the trial members will be inquired whether they concur with utilizing their information in case they withdraw from the trial. Additionally, their consent will be obtained by the research team to share relevant data with the scholarly specialists chosen from the universities or other administrative specialists. Notably, this trial does not include the collection of organic examples for storage.

## Interventions

### Explanation for the choice of comparators {6b}

The participants in the control group will receive the standard formulation of fat-soluble vitamins similar to the routine CF treatment; this is the reason for considering the routine CF treatment as the control group in our study.

### Intervention description {11a}

Nanomicelle fat-soluble vitamins (Exir Nano Sina Drug Company, Iran) are prepared as nanomicelle formation including 1500 units of vitamin A, 3000 units of vitamin D, 150 units of vitamin E, and 1000 μg of vitamin K in 1 cc of the drop. The nanomicelle formulation has been labeled by Exir Nano Sina Company, respectively, and will be administered orally alone or with sucrose-sweetened water once daily at bedtime at a daily dosage of 1 cc for 3 months.

### Criteria for discontinuing or modifying allocated interventions {11b}

Although no side effects have been reported in previous similar studies, in the event of any intervention-related side effects, we will stop the intervention and report the situation to the ethics committee of Mashhad University of Medical Sciences (MUMS) for making decisions [3]. Additionally, if the participants request to discontinue treatment or report the deterioration of their condition due to CF, we will stop the intervention.

### Strategies to improve adherence to interventions {11c}

The strategies include taking the medicine once a day versus several times, before bedtime to minimize interference with other common CF medications, and using an oral drop in comparison to soft gel for easier consumption by children. Individualized training of the patients and their parents will inform them of the necessity of the intervention complement for an optimal impact. If the study members use less than 70% of the drugs, it shows adherence deficits.

### Relevant concomitant care permitted or prohibited during the trial {11d}

CF patients who have a pancreatic deficiency require PERT for enzyme replacement. In this respect, we enrolled CF patients with gastrointestinal involvement; all the patients use CREON as a common treatment in addition to Omeprazole to facilitate maximal effectiveness. Inhaled beta2-agonists are prescribed to CF patients with moderate to severe lung disease twice a week. Also, CF patients who have *Pseudomonas* sp. infection are treated with the inhalation form of tobramycin. Constantly low-dose azithromycin treatment is used in our patients that has an anti-inflammatory effect in CF patients 6 years of age and older.

### Provisions for post-trial care {30}

There is no anticipated harm or compensation for involvement in this trial. However, the follow-up will be carried out via phone calls every 2 weeks to determine if there are any complications.

### Outcomes {12}

The primary outcome of the current trial is the measurement of the serum levels of fat-soluble vitamins once at the onset of enrollment and once at the end of the trial after 3 months.

The secondary outcomes are clinical criteria evaluation by the Shwachman-Kulczycki score (an index to evaluate the severity of the disease in CF patients, which includes general activity, physical examination, nutrition, and radiological findings), anthropometric assessment by the BMI *Z* score, and quality of life evaluation by using the CFQ (Health-Related Quality of Life in Children with Cystic Fibrosis) from the baseline to 3 months of the intervention (Fig. 1).

**Fig. 1 Fig1:**
[figure not shown]
Study design flow chart

### Participant timeline {13}

Nutritional suggestions will be given to all the patients and their parents and legal guardians based on the CF requirements and modifiable CREON dosing according to the level of dietary fat. Additionally, the patients or their parents completed the CFQ, depending on age.All anthropometric measurements (weight and height without shoes) will be performed under equal guidance using a digital scale (model: SECA).The primary and secondary outcomes of the treatment will be examined before and after 3 months of treatment. The clinical evaluation and follow-up will be carried out via monthly visits and phone calls with the patients.Approximately 6 mL of blood will be collected before and after 3 months from the beginning of the trial and centrifuged, with the serum separated from the sediment, and preserved at a minimum temperature of − 20 °C.

### Sample size {14}

Due to the lack of clinical trials on the evaluation of the efficacy of nanomicelle formulation of fat-soluble vitamins in children with cystic fibrosis, we use the researcher’s experience to estimate the sample size. According to this, about 60% of CF patients who use the routine formulation of fat-soluble vitamins are treated for vitamin D deficiency. It is estimated that the new method will increase the recovery rate by 30–40%. Considering alpha = 0.05 and power = 80%, the minimum required sample size in each group is estimated to be 33 people. By considering the 10% dropout rate for the sample, a total of 37 samples for each group was calculated. In total, 74 patients with CF are needed to be included in the randomization aspect of this research.

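### The 80% power at 33 per arm belongs to a vitamin D recovery proportion, not to the planned comparison of serum levels of four vitamins

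*Protocol article*

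**What the plan says.** Sample size {14} rests on the researchers' experience, because no earlier trial was available. It starts from the statement that "about 60% of CF patients who use the routine formulation of fat-soluble vitamins are treated for vitamin D deficiency", and continues: "It is estimated that the new method will increase the recovery rate by 30–40" per cent. With "Considering alpha = 0.05 and power = 80" per cent, it concludes that "the minimum required sample size in each group is estimated to be 33 people". Allowing for dropout, "By considering the 10% dropout rate for the sample, a total of 37 samples for each group was calculated", or 74 in total.

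Outcomes {12} defines something else: "The primary outcome of the current trial is the measurement of the serum levels of fat-soluble vitamins once at the onset of enrollment" and again after 3 months. The vitamins are A, D, E and K. The secondary outcomes are the Shwachman-Kulczycki score, BMI Z score and quality of life. Recovery from deficiency is in neither list.

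Statistical methods {20a} names t-tests, Wilcoxon and Mann-Whitney tests, and ANCOVA for the secondary outcomes. Qualitative variables are to be described by frequencies and percentages; no test is named for them.

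The inclusion criteria ask for "gastrointestinal and pulmonary involvement", among other things, but not for a deficiency of any vitamin at baseline.

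**The concern.** A power statement is valid for one outcome, one effect and one test. Here the outcome behind the number (a binary recovery rate for one vitamin) differs from the primary outcome (continuous levels of four vitamins), and the test behind it (two proportions) is not among those named. The protocol gives no SD and no mean difference for any serum level, so the 80% cannot be converted into a power for the planned test without further assumptions.

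Recovery also presupposes a child who was deficient at the start. Since entry does not require this, the number who can contribute to the stated calculation may be below 33 per arm.

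At stake is how readers weigh a non-significant result. They would take it as coming from a comparison with 80% power for an effect that was thought through, and for the primary comparison no such effect is stated.

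**Working it through.** **Inputs.** From Sample size {14}: alpha 0.05 (taken as two-sided; the protocol does not say), power 80%, control rate 60%, increase 30–40%, dropout 10%. No SD is given for any vitamin.

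**1. Reproducing 33.** Two proportions, pooled variance under the null, no continuity correction:

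n = [1.960·√(2·p̄(1−p̄)) + 0.842·√(p1(1−p1) + p2(1−p2))]² / (p2 − p1)²

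With p1 = 0.60, p2 = 0.90 and p̄ = 0.75: n = [1.960 × 0.612 + 0.842 × 0.574]² / 0.09 = 31.5, so 32 per arm. Power at 33 is 82%. Dropout: 33 / 0.9 = 36.7, so 37 per arm and 74 in total. The arithmetic is sound.

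**2. Which reading of the increase was used.** With 60% as the control recovery rate and a two-sided test:

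| Reading | Rates | n per arm |
|---|---|---|
| +30 points | 60% v 90% | 32 |
| +40 points | 60% v 100% | 15 |
| +30% relative | 60% v 78% | 103 |
| +40% relative | 60% v 84% | 54 |

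Only the lower end of the absolute reading fits. The sentence with the 60% is loosely worded. If it meant that 60% stay deficient, 40% v 70% gives 33 with a one-sided test but 42 with a two-sided one. That too would be a 30-point difference in a proportion, so the point does not depend on it.

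**3. What 33 per arm offers for the planned test.** Independent t-test, two-sided, noncentral t distribution:

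- Alpha 0.05: 80% power at a difference of 0.70 SD.
- Alpha 0.05 / 4 = 0.0125 (splitting over four vitamins is an assumption; the protocol applies 0.05 throughout): 80% power at 0.84 SD.
- Over an assumed range of true differences at alpha 0.05, power is 36% at 0.4 SD, 52% at 0.5, 67% at 0.6, 80% at 0.7 and 89% at 0.8.

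That 0.70 SD also leads to 33 per arm is coincidence; no such input is stated.

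**4. What the protocol's own assumption implies for vitamin D.** If levels are normal with equal SD (assumption), 60% and 90% above a common threshold correspond to a shift of 1.282 − 0.253 = 1.03 SD. The t-test at 33 per arm then has 98% power at alpha 0.05, and 94% at 0.0125.

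**5. Denominator for recovery.** Power for 60% v 90% by number deficient at baseline per arm (the numbers are assumptions): 13 gives 42%, 20 gives 60%, 30 gives 78%, 33 gives 82%.

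**The case against.** The strongest reply is that the calculation is correct and not far from the primary outcome. Serum vitamin D is one of the four levels, and Objectives {7} speaks of reaching an appropriate level, so recovery is a dichotomy of part of the primary outcome. Dichotomising usually costs power, so a trial sized for the proportion should be at least as strong for the level. This stands for vitamin D, as step 4 shows. It says nothing about vitamins A, E and K.

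It can also be said that a test of proportions may sit in an analysis plan that is not shown. That is possible. But the protocol does state its sample size, its primary outcome and its tests, and the first does not match the other two.

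Three stronger readings are tempting, and the documents do not support them:

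- *The trial is underpowered.* No SD or mean difference is given, so this cannot be shown, and step 4 points the other way for vitamin D.
- *The true requirement was 54 or 103 per arm.* Those figures come from a relative reading that does not reproduce 33, so they describe a calculation the authors did not make. What remains is loose wording of the increase.
- *Few children will be evaluable for recovery.* The protocol gives no baseline rate of vitamin D deficiency for its clinic. Its Discussion mentions about 90% of US patients with pancreatic insufficiency and fat-soluble vitamin deficiency. That is not vitamin D alone, but 90% of 33 is about 30 per arm, with 78% power.

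Nor would a null result be uninterpretable: the estimate and its confidence interval remain informative whatever outcome was used for planning.

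**Conclusion.** The point holds as a mismatch, not as an arithmetic error. The 33 per arm and the 80% describe recovery from vitamin D deficiency at 60% v 90%. They do not apply to the planned comparison of continuous serum levels, and vitamins A, E and K have no power basis at all. What 33 evaluable per arm does support is detection of 0.70 SD in one vitamin with 80% power, or 0.84 SD if alpha is split over four.

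These figures assume a two-sided t-test, equal SDs and 33 evaluable in each arm. The 98% for vitamin D rests further on normality and on the protocol's own recovery rates. Whether the trial has enough power for its primary outcome as a whole cannot be decided from the document.

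**What to change.** No further enrolment is needed.

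1. In Sample size {14}, write the assumption as *60% v 90%, absolute, recovery from vitamin D deficiency*, once the authors confirm that this was the calculation, and drop the 30–40% range.
2. State that the 80% refers to that proportion only. Give the detectable difference for serum levels at 33 evaluable per arm: 0.70 SD at two-sided 0.05, and 0.84 SD if alpha is split over four vitamins.
3. Add, declared as a supporting analysis, the proportion with vitamin D in the normal range at 3 months among participants deficient at baseline. Report the risk difference with its 95% confidence interval and the actual denominator. Table 1 is titled as listing normal ranges but is not visible in the text reviewed; confirm that it supplies one usable threshold.
4. Keep the four-vitamin primary outcome. Trial status gives recruitment as closed on November 30, 2022, and participants and the main researcher know the allocation. Narrowing the primary outcome to vitamin D at this stage would be a late change in an open trial, not a rewording.

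The cost is a rewritten paragraph and one analysis of data already being collected, approved as an amendment under {25} with its date relative to data access stated. The downside is that the stated power becomes less favourable, and the responder analysis may have fewer than 33 per arm.
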